**Figure 1 f1:**
[figure not shown]
Flow chart of the study protocol describing the two different phases.

• Prospective evaluation of clinical, electrophysiological, and peripheral biomarkers to predict the antidepressant response to ESK-NS and arTMS (n = 100).

• Integration of the above data with those previously collected from subjects with TRD treated with ESK-NS (n = 50) and arTMS (n = 50).

• Training a computerized system to develop a machine-learning-based tool that guides the treatment selection.

The subsequent stage (WP2; see **Figure 1**) focuses on the pilot validation of the ESK-NS and arTMS prescription using SelecTool, including the proof-of-concept estimation of SelecTool’s accuracy in an independent cohort (n = 20; out-of-sample validation). In this step, the identified biomarkers guiding treatment will be integrated into the SelecTool model as input data. Using the SelecTool’s output, individuals will undergo nonrandomized assignment to ESK-NS or arTMS interventions. Therefore, the accuracy in determining an increase in the number of responders to treatment will be estimated and compared with the response rates observed in random assignment.

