### Sample size and eligibility criteria

2.2

One-hundred and twenty subjects (WP1: 100 subjects; WP2: 20 subjects) who are diagnosed with major depressive episode (both during the course of MDD or bipolar disorder) according to the Diagnostic and Statistical Manual of Mental Disorders, 5th edition (24), will be recruited by three Research Units: the ‘G. d’Annunzio’ University of Chieti, the University of Milano, and the Tor Vergata University of Rome.

The inclusion criteria will be the following: age between 18 and 65; current major depressive episode within at least the past month; TRD, defined as the absence of clinical response despite two or more treatments with antidepressants at adequate doses for 4-6 weeks (5); current stable psychopharmacological therapy for at least 1 month.

The exclusion criteria will be the following: presence of severe organic or neurological comorbidities, any substance use disorder (except nicotine dependence) in the past 6 months, intellectual disability or decline (Mini-Mental State Examination, MMSE < 26); uncontrolled systemic hypertension (specific for safety of ESK-NS treatment); presence of a positive history of seizures in the patient’s history or a first-degree relative (specific for arTMS safety); pregnant and postpartum women.

To refine the processing precision of the tool, we will consolidate the dataset from participants enrolled in the study with clinical data gathered retrospectively. These supplemental data will be obtained from a dedicated TRD dataset, which includes information from subjects who met identical inclusion and exclusion criteria and underwent prior treatment in our centers with ESK-NS (n = 50) and arTMS (n = 50).

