### Statistical analysis

2.9

Drawing from the existing literature on the efficacy of arTMS and ESK-NS for Treatment-Resistant Depression (TRD), we anticipate a response rate of approximately 50% for each treatment (52, 57). The sample size was determined using the G*Power 3.1 software, taking into account specific parameters: a substantial effect size of predictors (expected Cohen effect size F = 0.4), power 1-beta = 0.80, one-way, four groups (2x2; treatment: ESK-NS, arTMS; responders and non-responders), and a significance level corrected for multiple comparisons (alpha = 0.001). These calculations resulted in a total sample size of n = 144. Considering a possible imbalance in the allocation of responders (10%) and to mitigate possible dropouts (10%), we increased the total sample size to n = 200.

We will develop a machine-learning model to predict the primary treatment outcome and use it for treatment guidance. This model will leverage both neurophysiological data and clinical scores. We also aim to interpret the model and extract the features that influence it. Given the heterogeneous nature of the collected data, an appropriate solution is to opt for ensemble methods, particularly random forest techniques, which have shown suitability for such tasks (19, p. 202) and are relevant for *post hoc* analysis of results. To provide comprehensive insights, our exploration will not be restricted to random forest techniques; we will also investigate other approaches such as neural networks or support vector classifiers. Dealing with missing values in clinical and psychometric tests is a critical concern, and we will address this using advanced techniques such as multivariate imputation (58, 59). The model parameters and performance will be assessed using nested and shuffle cross-validation, which is recognized as optimal to minimize bias in model error estimations (60). The results’ significance will be evaluated using permutation tests, which are acknowledged as the gold standard for statistical assessments of machine-learning algorithms (61).

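### The single sample size of 200 counts 100 earlier patients whose records are described as clinical data; on that description EEG and blood predictors have at most 100 patients and about 44–52% power, not 80%

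*Protocol article*

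**What the plan says.** Section 2.9 (Statistical analysis) gives one calculation for the whole project. Its inputs are:

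- effect: "a substantial effect size of predictors (expected Cohen effect size F = 0.4");
- power and layout: "power 1-beta = 0.80, one-way, four groups (2x2; treatment: ESK-NS, arTMS; responders and non-responders");
- significance level: "a significance level corrected for multiple comparisons (alpha = 0.001");
- group balance: "we anticipate a response rate of approximately 50% for each treatment".

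The result is stated as "These calculations resulted in a total sample size of n = 144". Allowances of 10% for imbalance in responders and 10% for dropout follow, and the total becomes 200 ("to mitigate possible dropouts (10%), we increased the total sample size to n = 200").

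Section 2.2 recruits 120 patients: 100 in WP1 and 20 in WP2. It then adds earlier patients from the centres, 50 per treatment, saying "we will consolidate the dataset from participants enrolled in the study with clinical data gathered retrospectively".

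In section 2.1, the list accompanying Figure 1 attaches the combined clinical, electrophysiological and blood evaluation to the prospective cohort: "peripheral biomarkers to predict the antidepressant response to ESK-NS and arTMS (n = 100"). The next item says that these data will be integrated with data collected previously from 50 patients per treatment. It does not name the type of those data.

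**The concern.** Section 2.9 speaks of predictors in general and gives them one size and one power. The predictors come from three sources: clinical scales, EEG and blood. If the earlier patients contribute clinical data, the 200 is available for clinical predictors, while EEG and blood predictors rest on the WP1 patients alone. That is below the 144 which the plan's own calculation requires.

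The shortfall would fall on the data types that motivate the project. The Discussion argues that the accuracy reached with symptom data alone is not enough for clinical use, and gives this as the reason for adding other biomarkers. A reader of section 2.9 would take 80% power as applying to them.

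**Working it through.** **Inputs.** From section 2.9: f = 0.4, four groups, alpha = 0.001, target power 0.80, dropout 10%. From sections 2.1 and 2.2: 100 WP1 patients, 20 WP2 patients, and 50 + 50 earlier patients. The 1:1 allocation (section 2.8) and a response rate near 50% per arm give four roughly equal cells.

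**Formula.** For the omnibus one-way F-test with four groups:

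- df1 = 4 − 1 = 3; df2 = N − 4
- noncentrality λ = f² × N = 0.16 × N
- power = P(F′(df1, df2, λ) > F crit), where F′ is the noncentral F and F crit is the upper 0.001 point of the central F(df1, df2)

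**Reproducing the plan's figure.** At N = 144, λ = 0.16 × 144 = 23.04 and power is 80.5%. The smallest total reaching 80% is 143, and 144 is the smallest with equal groups. This matches the plan. A test with one numerator degree of freedom would need 116 with equal groups, so the plan used the 3-df omnibus test.

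**What makes up the 200.** 100 (WP1) + 50 + 50 (earlier patients) = 200. No other combination of the stated counts gives it: all 120 recruited plus 100 earlier patients would be 220. The 20 WP2 patients are reserved for out-of-sample validation.

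**Power by number of patients with data on the predictor** (same f, groups and alpha):

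| N | Reading | λ | Power at f = 0.4 | f detectable with 80% power |
|---|---|---|---|---|
| 144 | plan's calculated size | 23.04 | 80.5% | 0.40 |
| 100 | WP1 patients only, no dropout | 16.0 | 52.3% | 0.48 |
| 90 | WP1 after 10% dropout (100 × 0.9) | 14.4 | 44.0% | 0.51 |
| 120 | WP1 plus the WP2 validation patients | 19.2 | 67.0% | 0.44 |
| 200 | all earlier records also hold EEG and blood | 32.0 | 95.7% | 0.34 |

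**Break-even.** To reach 144 for EEG and blood, 144 − 100 = 44 of the 100 earlier records would have to hold those data, or 144 − 90 = 54 after the stated dropout among WP1 patients.

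**The step from 144 to 200.** Two 10% allowances give 144 × 1.2 = 173, 144 × 1.1 × 1.1 = 174, or 144/(0.9 × 0.9) = 178. A total of 200 would correspond to a loss of 1 − 144/200 = 28%. Dropout in the usual sense applies to the prospective patients, not to records already collected.

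**The case against.** The strongest reply concerns the premise. Section 2.2 says clinical data; it does not say that there is nothing else. Section 2.1 speaks of integrating the prospective data, which include EEG and blood, with data collected earlier, and this leaves room for earlier recordings or samples. An article may also leave the contents of a retrospective dataset to the full protocol. This stands in part. It means that the 44–52% is conditional, and that a flat statement that the earlier patients have no EEG or blood data would go beyond the text. It does not remove the point: section 2.2 is the only place that names what the earlier records contain, no section says they hold EEG or blood, and the imputation described in section 2.9 is for clinical and psychometric tests.

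Second, the four-group F-test appears only in the sizing. The planned analysis is a machine-learning model assessed by cross-validation and permutation tests. This stands. A reader might infer that the study has only even odds of producing a working tool, or that a null EEG or blood result will be reported as absence of signal. The article supports neither: the power figures do not measure the model's accuracy, and no marker-by-marker test with such an interpretation is described.

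Third, a reader might take the unexplained rise from 144 to 200 as an error that weakens the study. It does not: 200 exceeds every version of the two allowances. Imbalance between responders and non-responders also removes no patients, so it should not be deducted from N as a loss.

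**Conclusion.** The point holds in conditional form. On the article's own description of its data sources, the single stated size and power do not apply to EEG and blood predictors. Those have at most 100 patients. Power for the plan's own effect is about 52%, or 44% after its own dropout allowance, against the stated 80%, and the detectable effect is about f = 0.48 or 0.51 instead of 0.40. For clinical predictors, with up to 200 patients, the stated power is met and exceeded.

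This rests on three assumptions: that the 200 is the 100 WP1 patients plus the 100 earlier patients, the only sum of the stated counts that fits; that the earlier records hold clinical data alone, as section 2.2 suggests but does not say outright; and that the four cells are roughly equal, as the anticipated response rates imply. If the second fails completely, power is about 96% and one clarifying sentence settles the matter. If only some records hold EEG and blood, the result lies between, with the break-even at 44 to 54 records.

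**What to change.** Revise the sample-size paragraph in section 2.9 as follows:

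1. State that 200 combines 100 prospective WP1 patients with 100 patients treated earlier.
2. State which data types the earlier records hold, and for how many patients, and make sections 2.1 and 2.2 agree.
3. Give N, with power or detectable f, separately for clinical predictors and for EEG and blood predictors. If the earlier records hold clinical data alone, the second entry is 100 enrolled and about 90 evaluable, with power of about 44–52% at f = 0.4, or a detectable f of about 0.48–0.51 at 80% power.
4. Say that these figures belong to the F-test used for sizing and not to the accuracy of the machine-learning model.
5. As a minor point, describe 200 as the available size, since two 10% allowances on 144 lead to about 173–178.

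The cost is a rewritten paragraph and a check of the earlier dataset. No patients are added, and randomisation, the primary outcome and the planned analysis do not change. If the earlier records are clinical only, the stated power for the biomarker aim becomes less favourable.

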This study aims to develop and preliminarily validate a computational system that integrates clinical, electroencephalographical, and peripheral marker data, thus creating a tool to inform the treatment of Treatment-Resistant Depression (TRD) called “SelecTool”. This tool is designed to support clinical decision-making by helping select personalized, tailored interventions. Using a machine-learning analysis of multi-channel data, the SelecTool will guide treatment selection towards ESK-NS or arTMS. This manuscript delineates the study protocol of the SelecTool project, a translational, multicentric investigation encompassing two distinct phases that aim to develop a machine-learning based tool to help guide clinicians in managing TRD.

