### Treatment administration

2.8

During the first phase (WP1), subjects will be randomly assigned in a 1:1 ratio to receive arTMS or ESK-NS. A stratified randomization approach with a four-block size will be implemented to minimize inadvertent bias. Stratification factors will include sex (male, female), age (expected cutoff 50 years old), depression severity (mild/moderate depression, MADRS ≤ 34; severe depression, > 34), and treatment site (Chieti, Milan, and Rome). The randomization process will be carried out by an investigator external to the study.

In the pilot validation phase (WP2), the extracted treatment-guiding biomarkers will be incorporated into the SelecTool model as input data. Subsequently, subjects will be allocated to esketamine or arTMS interventions based on the output of the SelecTool.

All subjects will undergo a comprehensive preliminary visit to assess potential contraindications to treatments. Qualified medical personnel, specifically trained to handle potential side effects and emergencies related to treatments, will administer ESK-NS and arTMS treatments.

Subjects in the ESK-NS group will be administered the drug according to the EMA guidelines (49). It will be supplied in a double-use nasal spray device containing 200 μl of vehicle solution (two sprays), each delivering 28 mg (14 mg ESK-NS base per 100 μl of spray). This dose will be administered twice a week for the first week, followed by 84 mg (three devices) administered twice a week for three weeks, resulting in a total of 1 month of treatment. Before initial administration, patients will be instructed to blow their nose (only before the first device is administered) and then assisted to recline their head 45° (semi-reclined position) during administration to enhance retention of the medication within the nasal cavity. Each ESK-NS session will be conducted by qualified personnel who closely monitor vital parameters (blood pressure, heart rate) before and at 45 and 90 minutes after treatment, following international safety guidelines (50).

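### Section 2.9 assesses SelecTool in WP1 as a predictor of response, not as a chooser of treatment; the only selection check is a nonrandomised WP2 comparison with 20 patients

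*Protocol article*

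**What the plan says.** The aim is selection. The Background states that "the SelecTool will guide treatment selection towards ESK-NS or arTMS".

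Section 2.9 sets the modelling task as response prediction: "We will develop a machine-learning model to predict the primary treatment outcome and use it for treatment guidance". On evaluation it says "The model parameters and performance will be assessed using nested and shuffle cross-validation", gives minimal bias in estimated model error as the reason, and adds that "significance will be evaluated using permutation tests". It names no treatment-by-marker contrast and no estimate of response under the recommended arm.

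Section 2.8 makes WP1 a randomised comparison: "subjects will be randomly assigned in a 1:1 ratio to receive arTMS or ESK-NS", stratified by sex, age, severity and site. Section 2.2 gives 100 patients for WP1. It also adds retrospective data on 50 patients per treatment, who are not stated to have been randomised.

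Section 2.1 supplies a second criterion. In WP2, an "independent cohort (n = 20; out-of-sample validation"), "individuals will undergo nonrandomized assignment to ESK-NS or arTMS interventions" according to the tool's output, and the increase in responders "will be estimated and compared with the response rates observed in random assignment".

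**The concern.** A prediction of response and a recommendation between two treatments are different outputs. The first asks who will respond. The second asks whether this patient is more likely to respond to one treatment than to the other. Cross-validated error and a permutation test on it address the first question. A model driven by general prognosis (less chronic illness, for example) would do well on both and give no reason to prefer either treatment.

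At stake is whether the main WP1 result supports the project's central claim. WP1's randomisation allows selection to be estimated directly and without confounding, and section 2.9 does not use it for that. The question is then left to the 20 patients of WP2.

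**Working it through.** **1. The plan's own figure.** Inputs from section 2.9: one-way test, four treatment-by-response groups, f = 0.4, alpha 0.001, power 0.80. With noncentrality f² × N = 0.16 × 144 = 23.04 on 3 and 140 degrees of freedom, power is 0.805. The stated N = 144 is reproduced.

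This test does not require a treatment difference. Take equal groups and a marker whose mean is +0.4 SD in responders and −0.4 SD in non-responders, the same in both arms. The SD of the four group means is 0.4, so f = 0.4 exactly, with no treatment-by-response interaction. If the marker is normal with equal variances, responders and non-responders differ by d = 0.8 and AUC = Φ(0.8/√2) = Φ(0.566) ≈ 0.71. At 50% response per arm, each patient's probability of response is the same under either treatment, so the gain from choosing is zero.

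**2. Prognostic-only marker over a range.** The slopes are assumptions; the 50% response per arm is from section 2.9.

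| Log-odds slope per SD | AUC | Accuracy | Gain from selection |
|---|---|---|---|
| 1.0 | 0.74 | 67% | 0 |
| 1.5 | 0.81 | 73% | 0 |
| 2.0 | 0.86 | 78% | 0 |

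**3. Simulation at N = 100** (10 features, 5-fold out-of-fold predictions).
- Random forest per arm, prognostic slope 1.5: mean AUC 0.70, prediction test passed in 93% of 110 runs, true gain 0.
- Same forests, prognostic slope 1.0 and a real interaction of slope 1.0: mean AUC 0.67, true gain over random 9 points. AUC was thus higher for the model with no selection value.
- Ridge logistic with treatment interactions, prognostic slope 1.2: mean AUC 0.67, test passed in 82% of 600 runs, true gain 0.

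The 93% is generous: the rank test used rejected in 17.5% of runs with no signal. The AUC and zero-gain results do not depend on that test.

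**4. The WP2 check.** At 50% response, SE = √(0.25/20 + 0.25/100) = 0.122. Against a fixed 50% instead, 15 of 20 responders are needed (exact one-sided alpha 0.021), with power 13%, 42% and 80% at true response of 60%, 70% and 80%.

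**5. The same quantity from WP1.** Under 1:1 allocation about half the patients receive the arm that the tool would have recommended. Random assignment averages the matched and unmatched groups, so gain over random = (matched − unmatched)/2. The SE of the difference is √(0.25/50 + 0.25/50) = 0.10, and of the gain 0.05. In simulation the SD of the difference was 0.124 to 0.128, so about 0.06 for the gain.

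Power, two-sided alpha 0.05, with random assignment at 50%:

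| True gain over random | WP2 (20 v 100) | WP1, SE 0.10 | WP1, SD 0.125 |
|---|---|---|---|
| 10 points (matched 60%, unmatched 40%) | 12% | 52% | 36% |
| 15 points (65%, 35%) | 22% | 86% | 67% |
| 20 points (70%, 30%) | 36% | 99% | 89% |

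The last column is Φ((difference − 1.96 × 0.125)/0.125). With 90 evaluable patients the third column becomes 47%, 82% and 98%. For 80% power the difference must be about 2.8 × 0.10 = 0.28, a gain of 14 points. With SD 0.125 it is 2.8 × 0.125 = 0.35, a gain of about 17 to 18 points.

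**The case against.** Two stronger readings are tempting, and the article supports neither.

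- A reader might infer that SelecTool is judged on prediction alone. Section 2.1 says otherwise: WP2 compares response under the tool with response under random assignment. A purely prognostic tool has zero expected gain there and would succeed only by chance or case-mix.
- A reader might infer that a significant permutation test releases the tool into WP2. No section makes WP2 conditional on that result.

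It can also be said that section 2.9 names neither an accuracy metric nor what is permuted, that a condensed article may leave this to a fuller document, and that the two-by-two layout and the references to treatment-guiding biomarkers show treatment-specific intent. The intent is clear. But the article does state the model's target, its performance criterion and its significance test, and none of them as stated measures a treatment contrast.

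A policy-value analysis has its own weakness. Permuting treatment labels tests whether treatment matters at all, so a rule that sends nearly everyone to the better arm can pass. In a simulation with no heterogeneity (100 patients, 10 noise features, 120 runs), such a test rejected in 6% of runs with 50% response in both arms, 16% at 60% v 50%, 34% at 60% v 40% and 68% at 65% v 35%. The Discussion quotes response rates from 40% to 60%, so this matters, and the remedy has to allow for it.

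Finally, the project presents itself as preliminary, and WP1's randomisation keeps the data available for this analysis. That lowers the severity but does not remove the gap.

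**Conclusion.** The point holds for WP1. Section 2.9's stated criteria are predictive, and a model with no ability to select can meet them. That zero gain is exact when a marker acts equally in both arms and the arms respond equally; the AUC range of 0.74 to 0.86 rests on assumed slopes.

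The only planned selection check is in WP2. It is nonrandomised and, read as a comparison with the earlier WP1 patients, non-concurrent. Its SE is about 12 points and its power about 12% and 36% for true response of 60% and 70%, assuming 50% in all 100 WP1 patients. The randomised WP1 data can estimate the same gain with an SE of about 5 to 6 points. That figure describes models trained within folds, not the final tool, and it is still too imprecise for small gains.

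This should be fixed, but it does not invalidate the design.

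**What to change.** Add to section 2.9, as the main WP1 measure of selection performance, the out-of-fold policy value in the 100 randomised patients:

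1. For each held-out patient, predict response under each treatment and record the recommendation.
2. Compare observed response between patients whose randomised arm matched the recommendation and those whose arm did not, with weights from the 1:1 allocation. Report the gain over random assignment with a confidence interval. The interval should allow for cross-fitting, since the simple binomial SE (0.10) was below the simulated SD (0.124 to 0.128).
3. Also report the gain over giving everyone the better single treatment, or a treatment-by-score interaction, so that an overall arm difference is not read as personalisation.
4. If treatment labels are permuted, respect all the section 2.8 stratification factors (sex, age, severity, site) and refit the whole pipeline each time.
5. Use the retrospective patients for training if wanted, but not for scoring.
6. Keep AUC or accuracy as secondary, and keep the WP2 comparison as a descriptive pilot.

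The cost is analysis wording, code and computing time; no extra patients are needed. The headline figure will probably look less impressive than a prediction AUC. Because 80% power needs a gain of about 14 points at best, the result should be presented as an estimate with its interval, not as a pass or fail.

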### Study schedule

2.3

The enrolled patients will undergo a comprehensive clinical examination as the initial step. Electrophysiological (EEG recordings) and peripheral biomarkers will be collected during this process. The administration of ESK-NS or arTMS will be determined according to the groupings of participants. Specifically, in the first phase, subjects will be randomly assigned to arTMS or ESK-NS. In the second phase, the extracted treatment-orienting biomarkers will be introduced in the SelecTool model as input data. Based on the SelecTool output, subjects will be assigned to the ESK-NS or arTMS interventions.

Baseline and 1-month follow-up assessments will include neuropsychological and psychiatric evaluations, behavioral assessments, neurophysiological data acquisition, and the collection of peripheral biomarkers.

After one month, the clinical response will be measured by a blind rater based on the MADRS score (> 50% reduction).

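### SelecTool is trained to predict response, but it must output which treatment suits the patient; a single pooled random forest on the full feature set would recommend at close to chance

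*Protocol article*

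**What the plan says.** Section 2.9 (Statistical analysis) describes one model and its target: "We will develop a machine-learning model to predict the primary treatment outcome and use it for treatment guidance". It describes the inputs as follows: "This model will leverage both neurophysiological data and clinical scores". The authors intend to "opt for ensemble methods, particularly random forest techniques", and add that "we will also investigate other approaches such as neural networks or support vector classifiers". They also plan to extract the features that drive the model. Performance is judged by nested and shuffle cross-validation with permutation tests. The same section states that "we anticipate a response rate of approximately 50% for each treatment".

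Section 2.1 gives the purpose of this step in WP1: "Training a computerized system to develop a machine-learning-based tool that guides the treatment selection". Section 2.3 says that in WP2 "the extracted treatment-orienting biomarkers will be introduced in the SelecTool model as input data", and then: "Based on the SelecTool output, subjects will be assigned to the ESK-NS or arTMS interventions". Section 2.8 repeats this allocation for WP2.

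No section describes a treatment-by-feature interaction, separate models per arm, a contrast between arms, or the step from a predicted response to a recommended arm.

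**The concern.** Predicting who improves and predicting which of two treatments suits a patient better are different problems. A marker that raises the chance of response equally under both treatments is useful for the first and useless for the second. A marker that favours ESK-NS in some patients and arTMS in others decides the second, yet it may show no overall association with response.

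The stated training target is the first quantity and the stated use is the second. With equal response rates in the two arms, treatment has no main effect. A pooled forest with treatment as one column among many therefore has little reason to split on it, and its predictions under the two options are nearly identical. The recommendation is the project's product and it allocates the WP2 patients. WP2 could end up testing a tool that barely distinguishes the treatments, even if real effect modifiers exist.

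**Working it through.** **The plan's own figure.** Section 2.9 gives n = 144 for a one-way comparison of four groups with f = 0.4, alpha = 0.001 and power 0.80. With noncentrality N × f², the smallest sufficient N is 143, or 144 for equal groups (144 × 0.16 = 23.04; power 0.805). The figure reproduces. It sizes comparisons of marker means across treatment-by-response groups and says nothing about the quality of recommendations, so that needs its own check.

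**Number of inputs (assumption).** The article gives no count. Counting named items in sections 2.4 to 2.7:
- 16 psychometric scales
- 6 cognitive measures
- 13 blood markers
- 12 connectivity values (6 region pairs × 2 bands)
- about 24 microstate metrics, if four classes are assumed
- at least 3 other EEG measures

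Sum: 16 + 6 + 13 + 12 + 24 + 3 = 74, so about 70 or more. The range examined is 10 to 150.

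**Simulation.** From the article: 1:1 allocation, about 50% response per arm, random forest. Assumed: two prognostic features (log-odds 0.5 per SD each) and one or three effect modifiers that together shift the log-odds by +b × z in one arm and −b × z in the other, with z standard normal and b = 1.0 (strong). The remaining inputs are noise. Each fitted tool is applied to new patients and scored by their expected response under its recommendation. Random assignment gives 50% and a perfect tool about 66%.

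Expected response with three modifiers:

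| Training n | Inputs | Pooled forest, treatment as one column | One forest per arm | Difference |
|---|---|---|---|---|
| 200 | 70 | 51.0% | 57.0% | 6.0 |
| 100 | 70 | 50.4% | 53.9% | 3.5 |
| 200 | 15 | 56.6% | 60.4% | 3.8 |
| 100 | 15 | 54.7% | 58.9% | 4.2 |

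As a share of the achievable gain (66 − 50 = 16 points), at n = 200 and 70 inputs the pooled forest keeps 1.0/16 = 6% and per-arm forests 7.0/16 = 44%. At n = 100 and 70 inputs the shares are 0.4/16 = 3% and 3.9/16 = 24%.

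**Why it happens.** At n = 200, 70 inputs and one modifier, treatment made up 0.2-0.3% of the pooled forest's splits. Its predictions for the two arms were exactly equal in 32-59% of patients. It chose the truly better arm in 54%, against 70% for per-arm forests and 78% for a forest given explicit treatment-by-feature columns.

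**Sensitivity.**
- Fewer inputs: with one modifier at n = 200, the pooled forest chose the better arm in 68-69% of patients at 20 inputs and 73% at 10. Per-arm forests reached 80% and 82%.
- Weaker modifier (b = 0.5, 60 inputs, n = 200): 50.8% response against 52.4% for per-arm forests, with a perfect tool at 58.8%.
- Another learner: a pooled support vector classifier with a treatment column chose the better arm in 64-70% at 20 inputs, 55-57% at 60 and 51-54% at 150.
- Direction: per-arm forests beat the pooled forest in every scenario.

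**Would feature extraction help?** Section 2.9 extracts features that influence the response model. In 30 simulated runs (n = 200, 70 inputs, top 15 kept by forest importance), a single modifier survived in 10% of runs, and three modifiers survived at a rate of 20%. Keeping 15 of 70 at random would retain 15/70 = 21%. After this selection the pooled forest chose the better arm in 52% (one modifier) and 55% (three), against 72% and 71% for per-arm forests.

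**Would the planned checks reveal it?** Cross-validation and permutation tests of response prediction can be passed on prognostic features alone. WP2 has 20 patients; the standard error of a 50% response rate is √(0.25/20) = 0.11, or 11 points.

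**The case against.** The strongest reply is that this is a condensed article. How treatment is coded, whether fitting is pooled or by arm, and how the recommendation is formed may be in the full protocol or analysis plan. The article also signals a treatment-specific aim: section 2.1 speaks of predicting response to each treatment, sections 2.3 and 2.8 carry treatment-guiding biomarkers forward, and the sample size uses a treatment-by-response layout. The learner is left open.

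Much of this stands, and it rules out two stronger readings. A reader might infer that treatment is left out of the model, so that no recommendation could follow. The input sentence does not support this: it also omits blood markers, which the article elsewhere makes part of the tool, so it is not a complete list. A reader might also infer that SelecTool is bound to allocate like a coin flip. That result needs a pooled forest and either about 60 or more inputs or features selected on response. The documents fix neither the pooling nor the count, and with 10-20 inputs chosen in another way the pooled forest does clearly better than chance.

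The large gains at n = 200 also assume 200 randomised patients, whereas only 100 are randomised. For a contrast trained on those patients, the n = 100 rows apply.

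What does not fall away is the stated target. The article is not merely silent: it names response prediction as the training task and makes that same model the source of guidance.

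**Conclusion.** The point holds in conditional form. Section 2.9 trains on response and uses the result to choose between treatments, without fixing how the arms are contrasted. Fitted as the text reads, as one pooled forest on about 70 or more inputs with equal response rates, recommendations would be near chance: 50-52% response, against 54-57% for per-arm forests with three modifiers and about 66% for a perfect tool. With 15 inputs the pooled forest reaches about 55-57% and per-arm forests 59-60%.

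The direction was the same in every setting examined; the size was not. It rests on an assumed input count, assumed strong modifiers with no main effect of their own, and a pooled fit. With weaker modifiers every method moves towards 50%. The training target should be settled before SelecTool is trained, because the tool then allocates the WP2 patients.

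**What to change.** In section 2.9, replace the sentence on the model with wording such as:

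*SelecTool is trained on the treatment contrast. The primary training set is the 100 randomised WP1 patients. We fit arm-specific models, a model with explicit treatment-by-feature terms, or a model for the transformed outcome 2(2A − 1)(Y − mean Y), where Y is response, A = 1 for ESK-NS and 0 for arTMS, and the allocation probability is the known 1/2. The recommendation is the sign of the predicted ESK-NS minus arTMS difference in response. Features are selected on this contrast within the cross-validation. A model of response alone is reported as a descriptive prognostic analysis.*

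One of the three approaches should be named as primary. The transformed outcome works because, under 1:1 randomisation, its mean given the features equals the difference in response probability between the arms. The 100 retrospective patients, whose treatment was not randomised in this study, should enter only an adjusted or sensitivity analysis.

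The cost is plan wording and some programming, with no new data. Three downsides should be stated:
- Contrast estimates are noisier and harder to interpret than a response model.
- The expected gain at n = 100 is modest. It was 3.5 and 4.2 points in the table above, and 52.7 − 50.8 = 1.9 points in a similar simulation with 115 inputs, so roughly 2 to 4 points.
- Restricting primary training to randomised patients gives up half of the planned 200.
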